# Evaluation of convalescent plasma versus standard of care for the treatment of COVID-19 in hospitalized patients: study protocol for a phase 2 randomized, open-label, controlled, multicenter trial

**DOI:** 10.1186/s13063-020-05011-9

**Published:** 2021-01-20

**Keywords:** COVID-19, Randomized, Controlled trial, Protocol, Convalescent plasma (CP), Antibodies, Neutralizing antibodies, Hospitalized patients

## Abstract

**Background:**

COVID-19 is a respiratory disease caused by a novel coronavirus (SARS-CoV-2) and causes substantial morbidity and mortality. At the time this clinical trial was planned, there were no available vaccine or therapeutic agents with proven efficacy, but the severity of the condition prompted the use of several pharmacological and non-pharmacological interventions.

It has long been hypothesized that the use of convalescent plasma (CP) from infected patients who have developed an effective immune response is likely to be an option for the treatment of patients with a variety of severe acute respiratory infections (SARI) of viral etiology. The aim of this study is to assess the efficacy and safety of convalescent plasma in adult patients with severe COVID-19 pneumonia.

**Methods/design:**

The ConPlas-19 study is a multicenter, randomized, open-label controlled trial. The study has been planned to include 278 adult patients hospitalized with severe COVID-19 infection not requiring mechanical ventilation (invasive or non-invasive). Subjects are randomly assigned in a 1:1 ratio (139 per treatment arm), stratified by center, to receive intravenously administered CP (single infusion) plus SOC or SOC alone, and are to be followed for 30 days. The primary endpoint of the study is the proportion of patients that progress to category 5, 6, or 7 (on the 7-point ordinal scale proposed by the WHO) at day 15. Interim analyses for efficacy and/or futility will be conducted once 20%, 40%, and 60% of the planned sample size are enrolled and complete D15 assessment.

**Discussion:**

This clinical trial is designed to evaluate the efficacy and safety of passive immunotherapy with convalescent plasma for the treatment of adult patients hospitalized with COVID-19. The results of this study are expected to contribute to establishing the potential place of CP in the therapeutics for a new viral disease.

**Trial registration:**

ClinicalTrials.gov NCT04345523. Registered on 30 March, 2020. First posted date: April 14, 2020.

**Supplementary Information:**

The online version contains supplementary material available at 10.1186/s13063-020-05011-9.

## Background

COVID-19 is a respiratory disease caused by a novel coronavirus (SARS-CoV-2) and causes substantial morbidity and mortality. At the time the study was planned, there were no vaccines to prevent COVID-19 or infection with SARS-CoV or therapeutic agent with demonstrated efficacy as specific treatment for COVID-19.

Convalescent plasma (CP) from infected patients who have developed an immune response is likely to be an option for the treatment of patients with a variety of severe viral diseases. This would include patients in the most recent epidemics with coronaviruses, SARS1 in 2003 and MERS in 2012, and potentially as well patients in the current COVID-19 pandemic. Despite suggesting safety and potential efficacy, the available evidence has the major limitation of being based on predominantly low-quality uncontrolled studies [1]. Here we present a summary of the rationale and justification for conducting a multicenter, randomized clinical trial of CP therapy in COVID-19 hospitalized patients.

Passive immunotherapy involves the administration of antibodies against a given agent to a susceptible individual with the purpose of preventing or treating an infectious disease caused by that agent. Historically CP has been used in outbreaks of poliomyelitis, measles, mumps, influenza (1918 H1N1 and 2009–2010 H1N1), and 2013 Ebola [2]. In addition, although less readily available and requiring more complex manufacturing than CP, conventional and hyperimmune immunoglobulins are used in clinical practice on a number of infections such as respiratory syncytial virus, hepatitis B, and others [3].

Currently, the only source of antibodies available for immediate use against SARS-CoV-2 is human CP. This is a readily available resource during an epidemic crisis even in low-income countries, as it uses the infrastructure and means developed for blood transfusions. In addition, as more individuals contract COVID-19 and recover, the number of potential donors will continue to increase in all areas where COVID-19 epidemic is present [4].

The experience with severe acute respiratory infections (SARI) caused by a coronavirus is rather recent in a number of epidemics in the twenty-first century. Human CP was used in patients from both SARS-1 in 2003 and MERS in 2012. Overall, the experience showed that CP is safe and likely to reduce mortality in patients with coronavirus-related SARI. The largest study with 80 patients with SARS in Hong Kong in 2003 [5] and subsequent publications [6, 7] point out that earlier administration after symptom onset is more effective, particularly before day 14, prior to seroconversion in patients remaining PCR test positive.

From this background and rationale, we have developed this study with the objective of evaluating the safety and efficacy of CP in hospitalized adult patients with severe COVID-19. In the midst of a worldwide pandemic of SARS-CoV-2 and COVID-19, CP was hypothesized to represent a potential effective therapeutic option with a favorable safety profile for these patients.

## Objectives

The trial objective is to evaluate the clinical efficacy and safety of Convalescent Plasma combined with standard of care (SOC) compared with SOC alone in adult patients with severe COVID-19.

## Study design

This is a phase 2, parallel group, randomized, open-label, controlled, superiority, multicenter clinical trial.

The protocol has been prepared in accordance with the SPIRIT (Standard Protocol Items: Recommendations for Interventional Trials) guidelines (Fig. 1).

**Fig. 1 Fig1:**
[figure not shown]

[figure not shown]

[figure not shown]
SPIRIT 2013 Checklist: Recommended items to address in a clinical trial protocol and related documents*

Approximately 278 patients (139 per arm) with severe SARS-CoV-2 pneumonia will be enrolled at 32 centers. Individuals fulfilling selection criteria will be randomized to receive CP (+SOC) or SOC alone at a ratio of 1:1. Also, approximately 140–200 CP donors will be recruited.

The study has been planned with a sequential design. Interim analyses for safety monitoring and for comprehensive efficacy/futility will be conducted when 20%, 40%, 60%, and 80% of patients have been recruited and completed D15 primary endpoint assessment, or at the discretionary criteria of the Data Safety Monitoring Board (DSMB) when needed.

## Methods: participants, interventions, and outcomes

### Participating centers

Study clinical sites included 33 public and private tertiary hospitals across the different regions in Spain. The only requirement for the participating study sites was a local research team that includes as co-principal investigators both a hematologist and an infectious diseases or internal medicine investigator, together with participation in the trial of the reference Transfusion Center. Transfusion services or centers at the hospitals or Autonomous Communities and National Army Transfusion Center are essential participants in this trial. ISCIII (Centro Nacional de Microbiología, Instituto de Salud Carlos III) centralized the antibodies and PCR microbiological testing from patients and donors (Additional file 1).

### Eligibility criteria

#### Eligibility criteria for patients

*Inclusion criteria are as follows:*
Written informed consent prior to performing study procedures. Witnessed oral consent will be accepted in order to avoid paper handling, which increased the risk of transmission of the infection. Written consent by patient or representatives will be obtained as soon as possible.Male or female adult patient ≥ 18 years of age at the time of enrolment.Laboratory-confirmed SARS-CoV-2 infection as determined by PCR in naso/oropharyngeal swabs or any other relevant specimen obtained in the ongoing COVID-19 symptomatic period. Alternative tests (i.e., rapid antigenic tests) are also acceptable as laboratory confirmation if their adequate specificity has been accepted by the sponsor.Patients requiring hospitalization for COVID-19 without mechanical ventilation (invasive or non-invasive) or high flow oxygen devices and at least one of the following:- Radiographic evidence of pulmonary infiltrates by imaging (chest X-ray, CT scan, etc.) OR- Clinical assessment (evidence of rales/crackles on exam) and SpO2 ≤ 94% on room air that requires supplemental oxygen.No more than 12 days between the onset of symptoms (fever or cough) and treatment administration day. Following 31 August amendment, only patients with no more than 7 days between the onset of symptoms and treatment administration day are allowed for inclusion.

*Exclusion criteria are as follows:*
Requiring mechanical ventilation (invasive or non-invasive) or high flow oxygen devices at screening.More than 12 days since symptoms (fever or cough) onset.Participation in any other clinical trial of an experimental treatment for COVID-19.In the opinion of the clinical team, progression to death is imminent and inevitable within the next 24 h, irrespective of the provision of treatments.Any incompatibility or allergy to the administration of human plasma.Stage 4 severe chronic kidney disease or requiring dialysis (i.e., eGFR < 30).

#### Eligibility criteria for donors

*Inclusion criteria are as follows:*
Subjects willing and able to provide written informed consent.Fulfilling all the current requirements to be a plasma apheresis donor according to the regulations for donation of blood products (European Guidelines and RD 1088/2005 in Spain).Absence of COVID-19 symptoms within the last 14 days.Anti SARS-CoV-2 IgG antibodies detectable in peripheral blood.≥ 18 years of age at time of donation.Weight > 50 kg and good vein access are standard criteria, for which exceptions could be considered according to the criteria of the blood bank and hematologist.

*Exclusion criteria are as follows:*
Plasmapheresis in the previous 7 days.Whole blood donation in the previous 30 days.Donation of more than 25 l of plasma in the previous 12 months.

#### Informed consent

Investigators will obtain the subject’s informed consent in accordance with Spanish Law 14/2007 on Biomedical Investigation and the internationally ethical accepted guidelines.

Patients will receive a concise and focused presentation of key information about the clinical trial, orally, and a written informed consent form will be handled to the patient. Due to paper handling limitation in COVID wards, oral witnessed consent will be accepted before entering into the trial, with written documentation in the patient clinical record. If possible, written consent form will be obtained from the patient himself or acceptable representatives, at a later time.

Donors will receive concise information about the clinical trial and will give written informed consent before donating convalescent plasma.

#### Additional consent provisions

The consent form includes provisions for research data and residual samples to be stored for future scientific research on COVID-19. These future studies will be previously evaluated by a Research Ethics Committee and will comply with the applicable ethical and legal requirements.

### Study interventions

#### Intervention description

All trial participants will receive SOC for COVID-19. The control arm is SOC for COVID-19. In the treatment arm, patients will also receive intravenous pathogen-reduced CP from patients recovered from COVID-19 (designated as donors) as add-on therapy to SOC.

In the current status of a worldwide pandemic for which we have no approved vaccines or drugs, for the purpose of this trial SOC will include any medicinal products being used in clinical practice (e.g., lopinavir/ritonavir; darunavir/cobicistat; hydroxy/chloroquine, tocilizumab, remdesivir, allowed as SOC when its use outside clinical trials was permitted), other than those used as part of another clinical trial.

Donor assessment, pathogen-reduced plasma collection, and production will be performed by hospital Transfusion Services and Regional Transfusion Centers. Local organization will be adapted to the existing structure at the regional level.

#### Criteria for discontinuing or modifying allocated interventions

A patient may be removed from the study treatment for the reasons mentioned below, although whenever possible the patient should be followed regardless of their protocol adherence as per the efficacy and safety evaluations:
Patient withdraws consent or requests discontinuation from the study for any reasonTermination of the study.Lost to follow-up.

Patients who withdraw from this study or are lost to follow-up after signing the informed consent form (ICF) will not be replaced. The reason for patient discontinuation from the study will be recorded on the appropriate case report form.

#### Strategies to improve adherence to interventions

This item is not applicable, since the active agent is administered intravenously by health care professionals in a single-dose administration.

#### Relevant concomitant care permitted or prohibited during the trial

This study seeks to investigate the effects of CP in addition to standard of care. All concomitant care and interventions are permitted other than concomitant administration of any other experimental treatment.

#### Provisions for post-trial care

No special arrangements for post-trial care are anticipated.

### Outcomes

#### Primary outcome measure

The primary outcome measure is the proportion of patients that progress to category 5, 6, or 7 (hospitalized severe disease or death categories) on the 7-point ordinal scale recommended in the Master Protocol of the WHO R&D Blueprint expert group, at day 15 (Table 1).

**Table 1 Tab1:** Ordinal scale for illness severity

1. Not hospitalized, no limitation of activities	
2. Not hospitalized, limitation of activities	
3. Hospitalized, not requiring supplemental oxygen	
4. Hospitalized, requiring supplemental oxygen by mask or nasal prongs	
5. Hospitalized, non-invasive ventilation or high flow oxygen	
6. Hospitalized, intubation and mechanical ventilation or ECMO	
7. Death	

#### Secondary outcome measures

The secondary outcome measures include the following:

-Ordinal scale (see 7-point ordinal scale above):
Status at day 30Time to category 5, 6, or 7 of the ordinal scale.Time to an improvement of one category from admission on the ordinal scale.Time to first deteriorationMean change in the ranking on an ordinal scale from baseline to days 3, 5, 8, 11, 15, 29, and 60.

-Ordinal scale of 11 points (Additional file 2):
Mean change in the ranking on an ordinal scale from baseline to days 3, 5, 8, 11, 15, 29, and 60Status at day 15 and 30Mortality rate (all cause) at day 15, at day 29, and at day 60.Oxygenation-free days in the first 28 days (day 29).Ventilator-free days in the first 28 days (day 29).Duration of hospitalization (days).Incidence of thrombotic arterial events.Incidence of thrombotic venous events.Rate of rehospitalizations.Serum level of CRP, lymphocyte count, LDH, D Dimer, IL-6, coagulation tests at baseline and at days 3, 5, 8, 11, 15, 29, and 60.Safety assessments of CP + SOC as compared to SOC alone through day 60 considering cumulative incidence of serious adverse events (SAEs), cumulative incidence of Grade 3 and 4 adverse events (AEs), and infusion-related adverse reactions.

#### Exploratory outcomes include the following virology and immunology assessments

Qualitative and quantitative RT-PCR for SARS-CoV-2 in nasopharyngeal/oropharyngeal swabs at baseline and at hospital discharge;Qualitative and quantitative RT-PCR for SARS-CoV-2 in blood on days 3, 5, 8, 11, 15, 29, and 60 (while hospitalized), until two of them are negative consecutively;Quantitative anti SARS-CoV-2 antibodies level at baseline and on days 8, 15, 29, and 60 (while hospitalized);Neutralizing antibodies study in plasma donors and a subset of patients at baseline.

### Participant timelines

The schedule of interventions and visits can be found in Fig. 2.

**Fig. 2 Fig2:**
[figure not shown]
Schedule of study procedures

### Sample size

We propose an open-label, standard of care controlled, randomized (1:1 ratio) clinical trial with stopping boundaries for efficacy and futility at 20, 40, 60, and 80% of the final sample size. The statistical design including the sample size and stopping have been calculated using the East validated software v6.5 by Cytel Inc. The stopping boundaries for superiority and inferiority have been calculated using the rho family spending functions.

The primary outcome measure is the proportion of patients that progress to category 5, 6, or 7 (hospitalized with severe disease or death categories of the 7-point ordinal scale), at day 15. With this design, 278 patients (139 per arm) will be required assuming 20% rate in the control group and an absolute reduction of 10% (10% rate in experimental group), with 80% statistical power and a 2.5% one-sided alpha level (5% two-sided). Likewise, approximately 140–200 CP donors will be needed.

With regard to the final sample size, it is predefined that a sample size recalculation will be put in place when 60% of the patients with assessed events at day 15 are available and the 3rd analyses are conducted.

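### The stated 278 patients give about 65% power, not 80%, for 20% versus 10% at one-sided 2.5%

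*Protocol article*

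**What the plan says.** The Sample size section gives every input to the calculation in one sentence:

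- number, and event rates for progression to category 5, 6 or 7 at day 15: "278 patients (139 per arm) will be required assuming 20% rate in the control group and an absolute reduction of 10" per cent, that is, "10% rate in experimental group";
- power and error rate: "with 80% statistical power and a 2.5% one-sided alpha level (5% two-sided".

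The same section places efficacy and futility boundaries at 20, 40, 60 and 80% of the final sample size, says the calculation was done in East v6.5, and predefines a sample size recalculation at the third analysis (60%). The Interim analyses section gives rho-family spending with rho = 7. Sequence generation gives 1:1 allocation. No dropout allowance is stated, and Methods to handle missing data expects very little missingness.

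The number recurs in the abstract ("The study has been planned to include 278 adult patients") and under Study design ("Approximately 278 patients (139 per arm) with severe SARS-CoV-2 pneumonia will be enrolled").

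**The concern.** For 20% versus 10% at one-sided 2.5% and 80% power, a trial statistician expects roughly 200 patients per arm. A figure of 139 per arm is too far below that to be a matter of formula or rounding.

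This is the power claim for the primary endpoint. Anyone reading a non-significant result will judge it against that claim. A trial believed to have 80% power for a halving of progression gives stronger evidence against such an effect than one with 65%. The stated power is also the natural reference for the recalculation at 60%, and for the Data Safety Monitoring Board, which may recommend a change of sample size.

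**Working it through.** **Inputs** (Sample size, unless noted): p1 = 0.20, p2 = 0.10, difference 0.10, n = 139 per arm, one-sided alpha 0.025 (z = 1.960), power 0.80 (z = 0.8416), 1:1 allocation (Sequence generation), rho = 7 (Interim analyses). The mean rate is 0.15.

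**1. Attempt to reproduce 139 per arm, fixed design**

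Pooled formula: n = [z_alpha·√(2·p̄(1−p̄)) + z_beta·√(p1(1−p1) + p2(1−p2))]² / (p1−p2)²

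= [1.960·√(2·0.15·0.85) + 0.8416·√(0.16 + 0.09)]² / 0.01
= [0.9897 + 0.4208]² / 0.01 = 198.96, so **199 per arm, 398 in total**.

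Other versions give these totals: unpooled 392 (196.2 per arm before rounding), arcsine 390, log odds ratio 414, log risk ratio 425, pooled with continuity correction 438. None is near 278.

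**2. Power at 139 per arm**

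Pooled: Φ{[0.10·√139 − 0.9897] / 0.5} = Φ{(1.1790 − 0.9897) / 0.5} = Φ(0.3785) = **64.7%**.

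Unpooled: 65.5%. Exact binomial power of the pooled z test: 65.5%. Arcsine: 65.8%. Log odds ratio: 63.1%. Log risk ratio: 62.0%.

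Run backwards, the pooled formula at 65% power gives 139.8 per arm, almost exactly the stated number.

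**3. Adding the sequential design**

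With rho = 7 almost no alpha is spent early. The efficacy boundaries at 20, 40, 60, 80 and 100% are Z = 4.98, 3.94, 3.20, 2.57 and 1.97. Numerical integration of the five-look design at 139 per arm gives 64.3% (pooled) to 65.3% (unpooled). Futility spending, binding or not, does not change this. The total needed for 80% power is:

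| Futility rule | Unpooled | Pooled |
|---|---|---|
| None | 396 | 404 |
| Non-binding | 396 | 404 |
| Binding | 392 | 400 |

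Smaller rho values make it worse: power at 278 is 57% to 63% for rho from 1 to 3.

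**4. Other readings of the stated inputs**

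- *One-sided 5%:* 157 per arm (314 in total) fixed, or 310 to 317 in total with looks. Power at 278 is 75% to 76%.
- *One-sided 10%:* 230 in total, or 268 with continuity correction.
- *278 as an expected rather than a maximum number:* with a maximum of 398 and the rho = 7 efficacy boundary, the expected total under the alternative is about 346.
- *Dropout:* an allowance would raise the number, not lower it.

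**5. What 278 does support at one-sided 2.5%, fixed design**

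With a 20% control rate, 80% power is reached at an experimental rate of about 8.3% (pooled), 8.4% (unpooled) or 8.5% (exact). By calculation alone, 25% versus 12% also gives 80.0% (pooled). The article does not suggest that either was intended.

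**The case against.** The arithmetic is not in dispute. The best case on the other side concerns what follows from it.

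*Which figure is wrong is not known.* The sentence shows only that number, rates, alpha and power are inconsistent. The East output is not shown, and a rate could have been misreported. This stands, and it is why the output has to be checked before the text is corrected. On the inputs as printed, however, the power claim is false.

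*The number is not final.* A recalculation is predefined at 60%, and the monitoring board may recommend changing the sample size, so final power need not be 65%. This also stands: the 35% miss rate applies only if enrolment stops at 278. It does not rescue the sentence, which presents 278 as the number required under the stated assumptions.

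*Interim looks can change the maximum.* With binding futility the required maximum can fall slightly below that of a design without such stopping. Here the effect is at most a patient or two per arm, against a gap of about 60 per arm.

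*The article condenses a longer protocol.* Nothing is claimed to be missing. All the inputs are printed, and no further detail can make 139 per arm deliver 80% power at these rates and this alpha.

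**Conclusion.** The point holds. On the plan's own inputs, 278 patients give about 65% power (62% to 66% across the test statistics and boundaries tried), some 15 percentage points below the stated 80%. For 80% power the design needs about 398 patients fixed, or about 392 to 404 with the stated looks, so 278 is about 30% short (278/398 = 0.70).

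This rests on the printed rates, alpha and allocation, with no dropout. The sequential figures also assume rho = 7 for both alpha and beta spending and looks at 20, 40, 60 and 80%. The abstract lists only the first three looks, but this makes no material difference: the fixed and five-look powers differ by less than half a percentage point.

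**What to change.** Retrieve or re-run the East calculation, archive its inputs and output, and establish which printed figure departs from it. Then correct the Sample size section so that number, rates, alpha and power agree. If 278 and the 20% control rate are confirmed, one of two statements will do:

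- 278 patients give about 65% power for 20% versus 10% at one-sided 2.5%; or
- 278 patients give 80% power for 20% versus about 8.3% to 8.5%, with the test method named.

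Use the corrected figure as the starting point of the recalculation at 60%.

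Either restatement is a change of wording only. It needs no extra patients, but the stated power or detectable effect becomes less favourable. If the sponsor instead wants to keep 80% power for 20% versus 10%, the target rises to about 398, which is 398 − 278 = 120 more patients. The number would then also change in the abstract and under Study design.

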##### Interim analyses

Interim analyses for comprehensive efficacy (or futility) and safety data monitoring analyses will be conducted when 20, 40, 60, and 80% of patients have been recruited and completed day 15 assessment, or at the discretionary criteria of the DSMB, when needed. The study may be stopped prematurely if either the efficacy or the futility boundaries are crossed. The boundaries will be adapted to the actual information rates in each inspection using the rho family spending functions (rho = 7) implemented in the East validated software v6.5 (or later releases) by Cytel Inc..

Ad hoc reviews will be undertaken at any time if there are other specific safety concerns. The study will not stop enrolment awaiting these DSMB reviews, though the DSMB may recommend temporary or permanent cessation of enrolment based on their safety reviews.

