### Composition of the data monitoring committee, its role and reporting structure

The independent DSMB in this study is responsible for reviewing the reports regarding the safety and efficacy of the study patients protocol adherence and making recommendations to continue or terminate the study or to modify the sample size of the basis of the results from the interim analysis. The DSMB members are all independent of the sponsor and have no financial or other conflict of interest.

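### The sample size may be changed from interim results at the 60% analysis, and the stated spending boundaries do not by themselves guarantee the one-sided 2.5% level if that change follows the observed effect

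*Protocol article*

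**What the plan says.** Four parts of the protocol article bear on this point.

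- **Sample size.** The design is set at 278 patients (139 per arm), "with 80% statistical power" and "a 2.5% one-sided alpha level (5% two-sided"). The section then declares as predefined that "a sample size recalculation will be put in place when 60% of the patients with assessed events at day 15 are available" and places this at the third analysis. It gives no rule, no cap, no direction of change, and no word on whether the recalculation is blinded.
- **Composition of the data monitoring committee.** The DSMB reviews safety and efficacy reports and may recommend stopping, continuing or "to modify the sample size of the basis of the results from the interim analysis".
- **Interim analyses.** The third analysis is one of the comparative efficacy and futility looks. Error control is described as follows: "The boundaries will be adapted to the actual information rates in each inspection using the rho family spending functions (rho = 7"). No other device is named.
- **Number of looks.** The abstract (Methods/design) says: "Interim analyses for efficacy and/or futility will be conducted once 20%, 40%, and 60% of the planned sample size are enrolled". The Study design text below Fig. 1 has looks "when 20%, 40%, 60%, and 80% of patients have been recruited". Sample size and Interim analyses also list four.

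**The concern.** A spending function evaluated at the actual information fractions keeps the type I error when the timing of looks does not depend on the observed treatment effect. A recalculation driven by comparative results breaks that condition: the final information becomes a function of the interim Z. If the usual statistic on all patients is then compared with the usual boundary, the rejection probability under the null depends on the recalculation rule and can exceed 2.5%.

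The primary test is at stake. The recalculation is also likely to be used, because 278 patients give about 65% power under the stated inputs (first step of the working). A positive result after a results-driven change might then not carry the error rate the article claims for it.

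**Working it through.** **1. The plan's own figure.** Inputs from Sample size: "assuming 20% rate in the control group and an absolute reduction of 10% (10% rate in experimental group"), one-sided 2.5%, 80% power, 1:1. With the pooled-variance formula, the number per arm is

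(1.960·√(2·0.15·0.85) + 0.842·√(0.16 + 0.09))² / 0.10² = (0.990 + 0.421)² / 0.01 ≈ 199, or 398 in total.

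The stated 278 is not reproduced. At 139 per arm, power is Φ((0.10·√139 − 0.990)/0.5) = Φ(0.378) ≈ 64.7%. With the rho = 7 looks included it is 65.4%. This is a separate matter and is used here only to show that pressure to change the size at 60% is built in.

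**2. Boundaries.** Spending is α(t) = 0.025·t⁷, so 0.0007 is spent by t = 0.6 and 0.0052 by t = 0.8. Looks at 20/40/60/80/100% give z-boundaries 4.98, 3.94, 3.20, 2.57 and 1.971. Looks at 20/40/60/100% give 4.98, 3.94, 3.20 and 1.962.

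**3. Null error after a change at 60%.** Let z be the statistic at t = 0.6 and R the new final size as a multiple of 278. If the ordinary statistic is kept, the null probability of rejecting at the end is

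A(z, R) = 1 − Φ((1.971·√R − z·√0.6) / √(R − 0.6)).

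The total error is P(Z > 3.201) + ∫ φ(z)·A(z, R(z)) dz over z < 3.201. The first term is 0.0007.

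Three values of z show the mechanism:

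- z = 0.5: A = 0.006 at R = 1 and 0.021 at R = 2. Enlarging a weak trial raises the null rejection probability.
- z = 1.5: A = 0.100 at R = 1 and 0.085 at R = 2. Enlarging a promising trial lowers it.
- z = 2.0: A = 0.252 at R = 1 and 0.492 at R = 0.62. Cutting a trial that is ahead raises it sharply.

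**4. Assumed rules.** The cap is R = 2 (556 patients). The target is 80% conditional power (CP) at the observed effect, where CP at R = 1 is 1 − Φ((1.971 − z/√0.6)/√0.4). CP of 10%, 30% and 80% corresponds to z of about 0.90, 1.27 and 1.94. The first column models the 60% look and the final analysis only. The second includes the 20, 40 and 80% looks with the z-boundaries kept. Futility is non-binding.

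| Rule at the 60% look | 60% + final | All looks |
|---|---|---|
| No change | 2.45% | 2.49% |
| Increase only if CP is 30–80% | 2.36% | 2.40% |
| Increase only if CP is 10–80% | 2.46% | 2.51% |
| Increase whenever CP is below 80% | 3.04% | 3.10% |
| Worst case, increases only | 3.14% | 3.21% |
| 80% CP rule, cuts to 0.62 allowed, increases only if CP ≥ 30% | 3.24% | not run |
| 80% CP rule, cuts to 0.62 allowed, no floor | 3.93% | not run |
| Worst case, cuts to 0.62 allowed | 4.29% | not run |

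With all looks, the worst case for increases is 2.97% at a cap of 1.5 and 3.64% at a cap of 4. Re-spending the boundaries on the new maximum barely alters these figures (3.20% instead of 3.21% at a cap of 2).

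**The case against.** The strongest reply is that the article does not say the recalculation is unblinded and does not say which statistic will be used afterwards. Both are inferences: the first from the DSMB's remit, the second from the absence of any method other than spending. The article defers detail to an SAP that is not shown, which may contain a rule, a cap and a weighted test. This stands as a limit on the claim. It does not remove the point, because the article itself fixes the time of the recalculation, its basis in interim results and the boundary method, and those three together do not secure 2.5%.

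A reader might go further and infer that the plan fails to hold the 2.5% level. The documents do not support that. A pooled-rate recalculation would have little effect on the error. Even an effect-based rule is harmless if the size only rises, and does so only at conditional power of about 10% or more. Nor does a promising-zone rule inflate the error here: material inflation from increases needs enlargement at z below about 0.9, which is an unpromising result.

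The figures with cuts assume something the article never describes, since the DSMB text speaks only of modifying the size. It does not rule cuts out either. The worst-case rows are upper bounds at each z and not rules that anyone has proposed.

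The look-count conflict should not be read as evidence of error inflation. Three places in the body agree on four looks, and the final critical value moves only from 1.962 to 1.971.

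**Conclusion.** The point holds as a lack of guarantee. Read together, Sample size and the DSMB section foresee a size change informed by interim results, and spending at actual information rates does not by itself protect the one-sided 2.5% if the new size depends on the observed effect.

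Under a cap of twice 278 and the ordinary statistic, the plausible error runs from no inflation (2.4–2.5%), through 3.0–3.1% for unrestricted increases, to 3.2–4.3% if cuts are permitted. Cap, target and floor are assumptions, because the article states none of them. The inflation is modest at most, but it concerns the primary test and is cheap to prevent, so the plan should be changed. The three-versus-four conflict is a real inconsistency of negligible numerical weight.

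**What to change.** **Preferred.** State that the 60% recalculation uses only the pooled, arm-blind day-15 event rate. Keep the target effect at its planned value, allow increases only and state a cap. Amend the DSMB remit so that it no longer provides for changing the size from comparative results. Cost: wording in the protocol and SAP. The downside is that such a rule cannot react to a treatment effect smaller than planned.

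**If a results-based change is kept.** State the rule and the cap. Combine the data before and after the recalculation with inverse-normal weights fixed from the 278 design, for example Z* = √0.6·Z₁ + √0.4·Z₂ at the final analysis. Here Z₂ comes only from patients after the 60% look. With the 80% look kept, the later part splits into two increments of weight √0.2 each. The original boundaries then hold the 2.5% level whatever size is chosen. The downside is a slight loss of efficiency, because the fixed weights no longer match the actual numbers of patients.

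**In either case.** Reconcile the abstract's looks at 20, 40 and 60% with the body's 20, 40, 60 and 80%. If four are intended, this is a one-line correction to the abstract.
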